### Safety assessment for early morbidity

When the safety analysis group reaches 484 patients, analysis will be performed to evaluate the safety of laparoscopic subtotal gastrectomy with D2 lymphadenectomy. Considering the reports of Sano et al. [11] and Deguili et al. [12], the complication rate of standard gastrectomy with D2 lymph node dissection was estimated at 20.9% and the margin of non-inferiority for the complication rate was assumed to be 12%. With a type I error of 0.025 (one-sided) and 90% power, 242 patients in each safety analysis group are required. When a total of 484 patients are enrolled in the safety analysis groups, the steering committee will decide whether this trial would be continued according to the results of this safety analysis.

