### Outcome measurements

The primary endpoint of the KLASS-02 RCT is non-inferiority in the 3-year relapse-free survival rate after laparoscopic subtotal gastrectomy and extended lymphadenectomy for locally AGC compared with open conventional surgery. To measure this endpoint, the criteria for recurrence are suggested in detail. Recurrence can be detected on regular follow-up studies such as abdominopelvic CT in patients without specific symptoms through a formal radiology report. If the results of follow-up studies are suspicious, whole-body positron emission tomography-CT, magnetic resonance imaging of the liver, or laparoscopic exploration can be performed to confirm recurrence. Otherwise, patients can attend follow-ups at shorter intervals than the planned schedule. Patients with specific symptoms, such as abdominal mass, weight loss, or intestinal obstruction, which might coincide with recurrence, should be evaluated for recurrence immediately regardless of the follow-up schedule. Surgeon should report recurrence in enrolled patients by entering this information into the eCRF as soon as the recurrence is confirmed.

Secondary outcomes include postoperative morbidity and mortality, postoperative recovery, and quality of life. Complications are divided into early and late morbidities depending on time of occurrence. Early morbidity is defined as surgery-related complications occurring within 21 days postoperatively, and includes the events listed in Table 2. Complication severity is classified according to grading system suggested by Dindo D et al. [10]. Regarding postoperative morbidity, the operative time and blood loss volume are also recorded. In cases of conversion from laparoscopic to open surgery, the reason for conversion should be explained. The events related to late morbidity, which occur after the 28th postoperative day, are listed in Table 2.

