The safety of laparoscopic D2 lymphadenectomy should be emphasized, because this study is the first multicenter RCT to evaluate its efficacy. In our RCT, morbidities related to surgeries will be investigated separately during early and late postoperative periods after surgery. Since most late complications such as reflux and intestinal obstruction are mainly related to reconstruction methods regardless of the type of laparoscopic or open laparotomy, we eventually focused on early postoperative morbidity to evaluate safety. When the number of patients recruited in this RCT reaches 484, the data related to early postoperative morbidities will be analyzed to determine whether laparoscopic surgery for D2 lymphadenectomy is less safe compared with open surgery. The number of patients required for this safety analysis was calculated according to previous RCTs, which reported that the complication rate of D2 lymphadenectomy was 20.9% in an RCT performed by Japanese surgeons, and the limitation of non-inferiority for complications of D2 lymphadenectomy compared with D1 was 12.0% in another Italian RCT [11,25]. This protocol includes a plan to stop recruitment and discontinue this RCT if the results of the safety analysis show significant inferiority in the safety of laparoscopic groups relative to the conventional group.

In conclusion, the KLASS-02 RCT was designed to show the efficacy of laparoscopic D2 lymphadenectomy in AGC patients compared with the open procedure. We attempted to highlight the principle of surgical clinical trials, and the internal validity of surgeons participating in this RCT was considered. Finally, we hope to suggest our RCT to other researchers who wish to conduct a well-designed, organized surgical clinical trial.

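### The only stated statistical criterion for the 484-patient continuation decision is an ungraded overall complication rate, so an excess of severe complications could go unseen although severity is already graded

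*Protocol article*

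**What the plan says.** The section Safety assessment for early morbidity sets out the decision in full. The look is triggered by a patient count: "When the safety analysis group reaches 484 patients, analysis will be performed to evaluate the safety". The reference value is one overall rate: "the complication rate of standard gastrectomy with D2 lymph node dissection was estimated at 20.9" per cent. For the tolerance, "the margin of non-inferiority for the complication rate was assumed to be 12" per cent. The size follows: "With a type I error of 0.025 (one-sided) and 90% power, 242 patients in each safety analysis group are required". As to the consequence, "the steering committee will decide whether this trial would be continued according to the results of this safety analysis".

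The Discussion describes the same look. It says that "the data related to early postoperative morbidities will be analyzed to determine whether laparoscopic surgery for D2 lymphadenectomy is less safe compared with open surgery", and that recruitment would stop if the results "show significant inferiority in the safety of laparoscopic groups relative to the conventional group".

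Outcome measurements defines early morbidity as surgery-related complications within 21 days and refers to Table 2 for the events. That list places wound infection and ileus beside leakage, intra-abdominal bleeding and pancreatitis or fistula. The same section states: "Complication severity is classified according to grading system". Neither description of the 484-patient look mentions the grade. Death is not on the Table 2 list; the text after that table has all deaths reported at once, with the cause recorded.

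**The concern.** A rate of patients with any complication gives a wound infection the same weight as an anastomotic leak. The test on that rate therefore answers whether laparoscopy produces more patients with some complication. It does not answer whether it produces more patients with a serious one. Severe events are normally a minority of the total, so a large relative increase in them moves the overall rate by only a few points, and the tolerance is 12 points. If minor events fell at the same time, the overall rate might not move at all.

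At stake is what the steering committee has in front of it when it decides on continuation. Up to 1,050 − 484 = 566 patients (54% of the planned total) are still to be enrolled at that point. The article collects the variable that would separate the two situations and then gives it no stated role.

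**Working it through.** **Inputs from the article (Safety assessment for early morbidity).** Open-arm complication rate p = 0.209; margin 0.12, read as an absolute difference because that reproduces the stated size; one-sided α = 0.025 (z = 1.960); power 90% (z = 1.282); 242 per arm.

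**Input that the article does not give.** The share of complications that are severe. I assume an open-arm severe rate s between 3% and 7%. A patient counts as severe if any complication is severe and otherwise as minor, so the two add up to the overall rate.

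**Step 1: the stated size.** n = (1.960 + 1.282)² × 2 × 0.209 × 0.791 / 0.12² = 241.3, hence 242 per arm, as stated. With SE = √(2 × 0.209 × 0.791 / 242) = 0.0370, power = Φ(0.12/0.0370 − 1.960) = Φ(1.286) = 90.1%.

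**Step 2: severe events double, minor events fall by the same amount.** The overall rate is 20.9% in both arms whatever s is. The calculation is that of Step 1: the non-inferiority test passes with probability 90.1%. A significant excess, which is the Discussion's wording for stopping, appears with probability 2.5%.

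**Step 3: severe events double, minor events unchanged.** The laparoscopic overall rate is 0.209 + s. With SE = √[(0.209 × 0.791 + pL(1 − pL)) / 242],

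P(pass) = Φ((0.12 − s)/SE − 1.960) and P(significant excess) = Φ(s/SE − 1.960).

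| Severe rate, open to laparoscopic (assumed) | Overall rate, laparoscopic | SE | P(pass) | P(significant excess) |
|---|---|---|---|---|
| 3% to 6% | 23.9% | 0.0379 | 66% | 12% |
| 5% to 10% | 25.9% | 0.0384 | 45% | 26% |
| 6% to 12% | 26.9% | 0.0387 | 34% | 34% |
| 7% to 14% | 27.9% | 0.0389 | 25% | 44% |

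A half offset lies between. For 6% to 12% with minor events down 3 points, the overall rate is 23.9%, the same as in the first row: 66% pass, 12% show a significant excess.

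**Step 4: what a direct comparison of severe events would see.** Same 242 per arm, one-sided 0.025, power = Φ(s/SE − 1.960) with SE = √[(s(1 − s) + 2s(1 − 2s)) / 242].

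| Severe rate (assumed) | SE | Power |
|---|---|---|
| 4% to 8% | 0.0215 | 46% |
| 5% to 10% | 0.0238 | 55% |
| 6% to 12% | 0.0259 | 64% |

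These powers do not depend on what minor events do. Under full offset they compare with 2.5% for the overall rate. With no offset the gain is smaller: for 6% to 12%, 64% against 34%.

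**The case against.** The case against has real force on several points.

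- **Nothing is miscalculated.** An overall early complication rate is a coherent safety endpoint, and its sample size is right. This stands; the point concerns what the endpoint can detect.
- **Full cancellation is an extreme.** The article gives no severe share and nowhere says that minor events will fall. This stands, and it is why the no-offset results are shown beside the full-offset one.
- **A reader might infer that a death counts the same as a wound infection.** The article does not support that. Death is not a Table 2 item, mortality is a separate outcome, and deaths are reported immediately with cause.
- **A reader might infer that the article itself shows severe events rising and minor ones falling with laparoscopy.** It does not. The Background mentions insecure bleeding control, but the Abstract lists lower operative blood loss as a benefit. The pancreatic-injury item in Table 1 belongs to D2 dissection in general, not to the laparoscopic approach.
- **Other safeguards exist.** An independent DSMC monitors the trial, the steering committee can review surgeons with frequent severe side effects, and the committee uses judgement. These reduce the risk but do not remove the point: as described, none is a between-arm criterion on severity. The full protocol or a charter may contain one, and its absence from an article is not in itself a fault. The article does, however, state this decision's endpoint, margin, error rate, power and size, and the endpoint stated is ungraded.
- **The added comparison is underpowered.** This stands and limits how its result may be read.

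**Conclusion.** The point holds as a limitation of a stated decision criterion, not as an error in the 484-patient figure. The overall rate with a 12-point margin can pass while severe complications have doubled. It does so with 90% probability under exact offset, and with about 66%, 45%, 34% or 25% probability with no offset at assumed open-arm severe rates of 3%, 5%, 6% or 7%. These results rest on normal approximations, on the absolute reading of the margin, and on severe rates and offsets that the article does not supply. They show what the criterion could miss. They do not show that severe complications are expected to be higher after laparoscopy. The change is worth making because the severity data are collected anyway.

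**What to change.** Add to the 484-patient analysis, in the protocol or the SAP, a prespecified comparison by arm of (a) patients with at least one severe complication and (b) deaths, both in the same early window as the overall rate. The investigators should fix the severity cut-off in advance on the grading system already in use. For each comparison give the difference with its 95% confidence interval and a one-sided 0.025 flag for harm. State that the steering committee must consider both beside the overall rate, and report them again at the final analysis. State also that absence of a flag is not evidence of safety, because power at 242 per arm is limited; the confidence interval should be read for the excess that it cannot exclude.

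**Cost.** One further analysis of data already recorded, with no added patients or visits. When the true rates are equal, each flagged comparison carries up to about a 2.5% chance of a false alarm (at most 2.5% + 2.5% = 5% for at least one of the two). The flag calls for consideration and does not itself stop the trial, so the practical cost of a false alarm is a closer look.

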### Interim analysis

When the number of target event as recurrent cases reaches half the expected number of the calculated sample size, we will perform an interim analysis to identify if clear evidence exists that laparoscopic surgery is inferior to open surgery, and should not be used. The interim analysis will be conducted by the Haybittle-Peto interim monitoring boundary method, with type I error set at 0.001 according to the previous report of Freidin et al. [13].

### Patient groups for statistical analysis

The efficacy for the primary and secondary outcomes will be evaluated in different groups of patients according to the surgical results. Except for the patients who are not undergoing surgery or have unresectable tumors, all patients will be included in the intention-to-treat (IIT) group. The postoperative recovery, morbidity and mortality, quality of life, and overall survival will be evaluated for the patients in IIT group. The 3-year relapse-free survival will be analyzed for patients in the full analysis set (FAS) group. ITT group patients who cannot undergo curative resection and have synchronous tumors or distant metastases un-defined at the screening step, will be additionally excluded from the FAS group. If patients did not comply with protocol because of various reasons like as conversion of surgical type, total resection and follow up loss, then they will be excluded from the per-protocol (PP) group. When the difference between the FAS and PP groups exceeds 10% of the total recruitment number, statistical analysis with the PP group patients will be performed. This RCT is schematically described in Figure 1. For safety analysis, patients in FAS group are examined with their actual treated surgery.

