## Background

Since the first laparoscopic gastrectomy for gastric cancer was performed in 1994 [1], increasingly more surgeons have performed this procedure in East Asian countries such as Korea and Japan [2]. Nevertheless, the Japanese Gastric Cancer Association (JGCA) treatment guideline recommends that laparoscopic surgery for gastric cancer should not be performed as a general practice [3]. The reason for this recommendation is that despite the benefits of laparoscopic surgery, the long-term survival results from 2 multicenter randomized clinical trials (RCTs) in Japan (registered in the University Hospital Medical Information Network [UMIN] Clinical Trial Registry as UMIN000003319) and Korea (registered in the National Institutes of Health [NIH] Clinical Trail Registry as NCT0045251) have not been reported. However, the interim analysis of a multicenter RCT conducted by Korean surgeons described the safety of laparoscopic surgery for early gastric cancer (EGC) [4]. In addition, several meta-analyses have showed that laparoscopic gastrectomy with limited lymphadenectomy for patients with EGC had non-inferior oncologic outcome relative to open surgery, and a benefit in terms of faster postoperative recovery [5-7]. Based on this evidence, most experienced surgeons have applied the laparoscopic procedure in patients with EGC.

However, the use of laparoscopic surgery in patients with locally advanced gastric cancer (AGC) remains controversial. Several obstacles have been considered as the reasons for this limitation. First, extended (D2) lymphadenectomy is an essential procedure for performing curative resection in AGC patients, which requires more sophisticated surgical techniques to ensure patient safety. Owing to some limitations of laparoscopic surgery such as impossible palpation, unsecure bleeding control, among others, the experience and skill of surgeons is more important in laparoscopic surgery for AGC. Second, some researchers have expressed the concern that the laparoscopic procedure for advanced malignant disease might aggravate cancer progression via the intraoperative intraperitoneal pressure and circulating gas. However, there is no conclusive evidence to support this hypothesis to date. Taken together, the application of laparoscopic surgery in patients with locally AGC is possible if the technical and oncologic safety is ensured.

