### Study protocol

The Ajou ARO (Academic Research Organization) in Ajou University Hospital will manage this clinical trial. As soon as the participating surgeons obtain informed consent from the patients, researchers entered the patient information into an web-based electrical clinical report form (eCRF;http://clintrial.ajoumc.or.kr/klass02/). The beta version of eCRF system tested at each actual site before full implementation, to ensure data capture system and to reduce user error. The eCRF system is automatically given screening number according to the sequence in which the informed consent forms are received. And if patients meet the criteria for a randomization, then eCRF system assigned at each surgery group.. Finally, the system provides an allocation number with a pre-generated randomized code for those who are selected by inclusion and exclusion criteria. A randomized block design is applied for randomization with each investigator as the stratification factor (R 2.10.1). To maintain the properties of randomization, block size is not open to the investigators. The surgeons are immediately notified of the randomization results via e-mail. After notification, the surgeons let the patients know which type of operation they will undergo. Therefore, the surgeon and patient blinding is impossible owing to the nature of surgical RCT. However, the protocol recommends that ward staff members evaluating patient outcomes be blinded, if possible. If the surgeon does not perform the operation within 30 days after recruitment, the patients are excluded from the trial. These patients will need to be re-evaluated for re-recruitment into this RCT.

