#### Laparoscopic procedure

Preoperative insertion of nasogastric tube is performed depending on each surgeon’s discretion. Prophylactic antibiotics are injected within 30 minutes before skin incision. The location and number of trocars are not limited. Surgeons will examine the abdominal cavity to determine whether there is no metastatic lesion or if the gastric cancer is resectable. If the patient has unexpected metastatic lesions or the surgeon decides that curative resection of tumor is impossible, the operation is stopped and the patient is excluded from this RCT. Washing cytology could be performed by inserting 50 cc of saline solution into the pelvic cavity. Then, the surgeon begins the D2 lymphadenectomy including total omentectomy. The guideline for D2 lymphadenectomy in locally AGC patients is shown in Table 1. If surgeons make an additional abdominal incision to control bleeding or for any other reason before finishing the laparoscopic D2 lymphadenectomy, they will record this situation as “conversion to open” in the eCRF system. After lymphadenectomy, the reconstruction methods are not limited in this RCT. The surgeon can perform one of the Billroth-I, Billroth-II, or Roux-en Y methods for reconstruction, which can be carried out by minilaparotomy. Hand-sewing or using staplers for anastomosis are not limited, and drain insertion is left to the discretion of each surgeon.

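### The set called intention-to-treat, used for overall survival, and the primary relapse-free survival set both drop randomised patients after the arm is known

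*Protocol article*

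**What the plan says.** The order of events is set out in the Methods of the protocol article.

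- **Allocation is known before surgery.** Under Study protocol: "The surgeons are immediately notified of the randomization results via e-mail" and "After notification, the surgeons let the patients know which type of operation they will undergo". The same section accepts the consequence: "Therefore, the surgeon and patient blinding is impossible owing to the nature of surgical RCT".
- **Exclusion before the operation.** Also under Study protocol: "If the surgeon does not perform the operation within 30 days after recruitment, the patients are excluded from the trial". Such patients may be re-evaluated for entry.
- **Exclusion during the operation.** Under Laparoscopic procedure, if unexpected metastases are found or the surgeon judges curative resection impossible, "the operation is stopped and the patient is excluded from this RCT". Open conventional procedure describes the open operation as similar, apart from lymphadenectomy under direct view.
- **The set called intention-to-treat.** Under Patient groups for statistical analysis: "Except for the patients who are not undergoing surgery or have unresectable tumors, all patients will be included in the intention-to-treat (IIT) group". Recovery, morbidity and mortality, quality of life and overall survival are analysed in this set.
- **The primary set.** In the same section: "The 3-year relapse-free survival will be analyzed for patients in the full analysis set (FAS) group". The FAS is the previous set less patients without curative resection and with synchronous tumours or distant metastases not identified at screening. The sentence does not make clear whether one of these grounds is enough or several are needed together.
- **The stated principle.** The Discussion lists intention-to-treat analysis among the general principles that the protocol follows as closely as possible. It explains the lack of blinding but not the departure from intention-to-treat.

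**The concern.** Randomisation protects a comparison only if patients stay in the analysis as allocated. Here patients leave after both surgeon and patient know the arm. Some leave before any operation (no surgery, or the 30-day rule). Others leave because the operating surgeon, working through the approach under test, judges the tumour unresectable or finds spread.

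If such exclusions fall unequally between the arms, the remaining groups differ in prognosis. A patient whose spread is recognised leaves the analysis; a similar patient in the other arm whose spread is not recognised stays and probably relapses early. In a non-inferiority trial this can work either way: it can make an equal laparoscopic operation look worse, or hide a real deficit.

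Overall survival is affected as well. It needs no curative resection to be defined, so there is less reason to analyse it in a reduced set.

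**Working it through.** **1. The plan's own figure.** Inputs from Sample size calculation: margin HR 1.43, 90% power, 1:1 allocation, 330 events, hazard rate 0.11. One-sided alpha is printed as 0.25.

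- Schoenfeld events: 4 × (z_alpha + z_power)² / (ln 1.43)².
- At alpha 0.025: 4 × (1.960 + 1.282)² / 0.3577² = 328.5, so 329. This agrees with 330.
- At the printed 0.25 the same formula gives 120. Alpha is therefore taken as 0.025 below.
- Three-year RFS: exp(-0.11 × 3) = 0.719, which agrees with the stated 72%.
- With 330 events, SE(ln HR) = 2/√330 = 0.1101. Power at a true HR of 1 is Φ(0.3577/0.1101 - 1.96) = Φ(1.289) = 90.1%.

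**2. Who leaves each set.**

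| Set | Used for | Randomised patients removed |
|---|---|---|
| Called intention-to-treat | Overall survival, morbidity and mortality, recovery, quality of life | No surgery; unresectable tumour |
| FAS | Primary RFS | The above, plus non-curative resection, synchronous tumours or metastases not seen at screening |
| Per-protocol | RFS, only if it differs from the FAS by more than 10% of recruitment | The above, plus conversion, total resection, loss to follow-up |

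Each set is contained in the one above it. The article names no set of all randomised patients.

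**3. Illustration of sensitivity.** The article gives no exclusion rates. Assume that a net share x of patients with occult disease stays in one arm but is removed from the other, and that all of them relapse within 3 years. With 525 per arm, x = 1-3% is about 5-16 patients. If the operations are truly equal:

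Observed HR = ln[(1 - x) × 0.719] / ln(0.719)

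- *Surplus in the laparoscopic arm, true HR 1:* power = Φ[(ln 1.43 - ln HR)/0.1101 - 1.96].
- *Surplus in the open arm, true HR 1.43, with the same shift applied in favour of laparoscopy:* type I error = Φ[ln HR/0.1101 - 1.96].

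| x | HR shift | Power | One-sided type I error |
|---|---|---|---|
| 0 | 1.000 | 90.1% | 2.5% |
| 1% | 1.030 | 84.5% | 4.6% |
| 2% | 1.061 | 77.3% | 7.8% |
| 3% | 1.092 | 68.7% | 12.3% |

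The last two columns are alternatives; they cannot both occur.

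**4. Check with a milder assumption.** If the occult-disease patients instead relapse at an assumed hazard of 0.7 to 1.4 per year, a Cox model over 3 years gives HR shifts of 1.03-1.10 for x = 1-3%. Power is then 85-67% and type I error 4-14%. The result does not depend on the extreme assumption in step 3.

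**5. Dilution in an all-randomised analysis.** If 3% of both arms count as events at operation and the true HR is 1.43, the same method gives ln[0.97 × 0.719^1.43] / ln[0.97 × 0.719] = (-0.502)/(-0.360) = 1.39. With 5% it is 1.37. False non-inferiority at the margin in that set would be about 4% and 6%.

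**The case against.** The strongest defence is that RFS presupposes a curative resection. Outcome measurements defines the endpoint as following gastrectomy and lymphadenectomy, and most excluded patients have disease that, had it been known, would have failed the entry criteria. If exclusions are balanced, little bias follows. This stands as a reason to keep the FAS for the primary analysis. It does not justify the intention-to-treat label, and it does not extend to overall survival.

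A reader might infer that the protocol itself shows laparoscopy to be worse at finding occult spread, because the Background says: "Owing to some limitations of laparoscopic surgery such as impossible palpation, unsecure bleeding control, among others". The text does not support that. Palpation and bleeding control are named there as technical obstacles that make surgeon skill important; nothing is said about detecting metastases. Unequal detection is possible but undocumented. Nor are all exclusions findings of the surgeon during surgery: having no surgery and the 30-day rule act before it.

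It may also be said that sensitivity sets and reporting of exclusions belong in the full protocol or analysis plan, which are not shown. That is fair, and the absence of an all-randomised analysis from the article does not prove that none is planned. The definition of intention-to-treat and its use for overall survival are, however, stated in the article, and that is what the point rests on.

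Finally, an all-randomised RFS analysis with immediate events in both arms is diluted towards 1, which is anti-conservative for non-inferiority. This also stands, and it limits the role such an analysis should have.

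**Conclusion.** The set labelled intention-to-treat is a modified intention-to-treat set, and the article uses it for overall survival, an outcome defined for every randomised patient. The primary RFS set is narrower still. Because all exclusions follow randomisation with the arm known, and some depend on the unblinded surgeon's judgement, the comparison is not fully protected by randomisation.

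The document does not show that bias exists, how large it would be, or which way it would run. The figures (HR shift of about 3-9%, power of about 85-69%, or type I error of about 5-12%) rest on an assumed net imbalance of 1-3%, on relapse of all those patients within 3 years, and on alpha of 0.025. They show that a difference of a few patients per arm would matter against a margin of 1.43, no more. It would go too far to conclude that the primary result will be biased, or that the FAS is unsuitable for the primary analysis.

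**What to change.** - Define intention-to-treat as all randomised patients by allocated arm, and use it for overall survival.
- Rename the current set modified intention-to-treat.
- Keep the FAS for the primary RFS analysis, and reword its exclusion sentence so that it is clear whether one ground suffices.
- Pre-specify an all-randomised RFS sensitivity analysis with time zero at randomisation, counting unresectable, metastatic or non-curative disease as an event at the operation date.
- Report exclusions by arm and reason.

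The cost is one extra analysis and survival follow-up of the few patients now dropped. Part of that may already be in place, since Outcome measurements has deaths among all recruited patients reported. Sample size and events are unchanged. Because the all-randomised RFS estimate is diluted towards 1, it should support the FAS result and neither replace it nor become a second success criterion; the joint power of a two-set rule has not been worked out.
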